### Primary outcome analysis

The target sample size is 120 randomized participants (60 per study arm). The sample size was based on our most recent IPS study at the Tuscaloosa VA Medical Center that evaluated IPS in the primary care setting as nearly half of the participants had a SUD diagnosis. We expect that more than 84% will complete the intervention as randomized and greater than 95% will provide analyzable employment data. The between-group effect size was 0.55 in favor of IPS in the prior study, for which our projected sample size (54 per group with > 2 months data) would provide > 81% power. Very conservatively assuming that only 90% provide analyzable data this yields approximately 54 participants per group. This provides 80% power to detect a difference in means between groups of 0.54 standard deviations for a continuous outcome. The primary employment outcome is the number of weeks with competitive employment over the 18-month follow-up period. A week scored as “worked” is one in which a competitive job was held for any number of hours or days during that week. A week scored as “not worked” is one in which there was no competitive job held, or there were no employment data (i.e., early exit or missing data). The analysis of the primary outcome will use longitudinal mixed-effects regression models considering the cumulative number of weeks worked at each assessment as the dependent variable and study arm (IPS vs. non-IPS-VR) as the main independent variable adjusted for gender. Study site will be treated as a random effect, as will participant to account for the nesting of participants within sites and the multiple observations per person. We will initially specify the covariance structure of the repeated outcomes as unstructured and will proceed respectively to autoregressive and exchangeable structures if convergence issues are encountered. Prior to final modeling we will examine longitudinal plots of the employment data by group to evaluate whether the most appropriate model and any possible interaction effect appears to be additive (linear regression) or multiplicative (suggesting negative binomial regression), whether time should be included as categorical or linear, and whether it appears that a group*time interaction term is required to faithfully model the data.

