The primary hypothesis that participants randomized to IPS will work more weeks over the 18-months compared to those randomized to non-IPS-VR will be evaluated using predicted marginal means (i.e., LS-means) to estimate the difference in hours worked and test significance at the *p* < 0.05 level. Adhering to the principle of intent-to-treat, participants may discontinue the treatment intervention, but will be encouraged to remain in the study for outcome assessments for the 18-month follow-up period and will be analyzed as-randomized.

The exploratory employment outcome is the dichotomous classification of whether each participant is a ‘steady worker’ operationalized as a participant who holds a competitive job for at least 50% of the 18-month follow-up period. The analysis for this outcome will follow the same structure as for the primary employment outcome but using logistic rather than linear regression. Similar analyses for overall intervention effects will also consider outcomes of total time worked (days and hours), income earned from competitive sources, and the type and number of jobs held. These analyses will be descriptive and will be used to identify the overall time-trends of employment between the groups, including when the highest probability of employment is reached and whether the efficacy appears to decline after a period of time. This information can be used to further refine future IPS interventions to maximize the durability of intervention effects.

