### Secondary outcomes analysis

The effect of treatment on each of the psychological clinical measures will be analyzed using a longitudinal mixed-effects regression model similar to the methods described above to model the longitudinal trends in employment outcomes. The dependent variable will be the outcome score at baseline and each follow-up time point. Each follow-up visit will be categorized by the weeks since enrollment and an indicator for calendar month when the visit occurred will also be included in the model to control for seasonality. We will formally test for differences in outcomes at 18 months using predicted-marginal means. All hypothesis tests are pre-specified so there is no compelling reason to adjust the alpha level for multiple comparisons, and because they are likely to be correlated, a Bonferroni correction would be expected to be overly conservative. However, to aid interpretation we will use the Benjamini–Hochberg method to control the family-wise false-discovery rate for the secondary outcomes to be ≤ 10%.

Both between-treatment condition and within-treatment condition effect sizes for primary and secondary outcomes will be presented: Cohen’s *d* for continuous outcomes and the number needed to treat for dichotomous outcomes. An estimate of the 95% confidence interval will accompany each effect size in order to guide interpretation. Effect sizes indicate the magnitude of the treatment effect based on clinical significance and are independent of sample size and hence statistical significance.

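### The form of the primary model is settled only after viewing outcome plots by arm, and the tested time point is not named, so the 5% error rate is not guaranteed

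*Protocol article*

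**What the plan says.** The Primary outcome analysis section of the protocol article fixes much of the primary model. It is a mixed model for the running total of competitive weeks at each assessment, with arm as the main predictor, adjustment for gender, and random effects for site and participant. The covariance is unstructured first, with simpler structures only if the model does not converge. Weeks without employment data count as not worked.

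Three features are left open. The text says "Prior to final modeling we will examine longitudinal plots of the employment data by group to evaluate whether the most appropriate model" is additive (linear) or multiplicative (negative binomial). The same inspection is to settle whether time is categorical or linear, and whether an arm-by-time "interaction term is required to faithfully model the data".

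The hypothesis is then evaluated with predicted marginal means, using these to "test significance at the *p* < 0.05 level". No visit is named for those means. Month 18 is named as the tested time point only in the Secondary outcomes analysis section, for the psychological measures.

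**The concern.** Plots by arm show the treatment contrast itself. Judging from them whether an arm-by-time term is needed means looking at the effect before deciding how to test it. The article does not merely leave the model form to another document: it states a procedure for choosing it, and that procedure uses the outcome by arm.

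The choice also decides what is estimated. The primary outcome is weeks worked over 18 months, which is the cumulative total at month 18. A model with an arm-by-visit term can estimate that difference. A model without it estimates one common shift across the totals at months 2 to 18. A negative binomial model estimates a ratio, while the sample size rests on a difference in means. At stake are the error rate of the only primary test and the meaning of its estimate.

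**Working it through.** **The plan's own figure.** Inputs from Primary outcome analysis: "The target sample size is 120 randomized participants (60 per study arm"); "Very conservatively assuming that only 90% provide analyzable data this yields approximately 54 participants per group" (60 × 0.90 = 54); effect size 0.55 with "54 per group with > 2 months data) would provide > 81% power"; and 80% power at 0.54 SD. Sidedness is not stated, so two-sided 0.05 is assumed.

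Power ≈ Φ(d√(n/2) − 1.96):
- d = 0.55: 0.55 × √27 − 1.96 = 2.858 − 1.960 = 0.898, giving 81.5% (noncentral t: 80.8%).
- d = 0.54: 2.806 − 1.960 = 0.846, giving 80.1% (noncentral t: 79.4%).

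The stated power is reproduced. It belongs to one fixed comparison of two means.

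**Type I error, inputs.** From the documents: 60 per arm, nine post-baseline visits (months 2 to 18), cumulative weeks, missing weeks scored as not worked (so every participant has all visits), alpha 0.05. Assumed: 78 weeks and a weekly in-job/out-of-job process identical in both arms, in three settings.

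| Assumed setting | A | B | C |
|---|---|---|---|
| Able to obtain a job | 60% | 100% | 50% |
| Mean weekly start rate | 0.03 | 0.02 | 0.05 |
| Weekly job-loss probability | 0.02 | 0.03 | 0.01 |
| Resulting mean weeks at month 18 | 17.3 | 20.0 | 20.8 |
| Resulting SD | 24.6 | 22.5 | 28.6 |
| No week worked | 58% | 39% | 60% |

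There were 5,000 null trials per setting, so the Monte Carlo SE is √(0.05 × 0.95 / 5000) ≈ 0.3 points. Participant-level equivalents stood in for the full mixed models, without site or gender:
- Visit average, month-18 total, and linear-time prediction at month 18 (weights 1/9 + 4c/60, with c = visit number − 5): pooled two-sample t-tests.
- Ratios: log of the ratio of arm means, with SE² the sum over arms of s²/(n × mean²).
- Common arm effect, unstructured covariance S: 1′S⁻¹(difference in visit means) / 1′S⁻¹1, with variance (2/n) / (1′S⁻¹1).

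The visual rule was represented by keeping the arm-by-time term if the arm difference in slope had p below 0.05, 0.10, 0.20 or 0.30. The slope served only to trigger the choice and was not itself tested as an outcome.

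| Rejection rate under the null (%) | A | B | C |
|---|---|---|---|
| Fixed: visit average | 5.3 | 5.3 | 5.2 |
| Fixed: month-18 difference | 5.2 | 5.5 | 5.3 |
| Fixed: linear-time prediction at month 18 | 5.1 | 5.5 | 5.2 |
| Fixed: ratio, visit average | 4.8 | 4.7 | 4.4 |
| Fixed: ratio, month 18 | 4.7 | 4.9 | 4.5 |
| Fixed: unstructured common effect | 5.7 | 6.4 | 6.7 |
| Rule: month 18, otherwise visit average | 5.2–6.1 | 5.5–6.5 | 5.3–5.8 |
| Rule: month 18, otherwise unstructured common effect | 8.9–10.5 | 10.1–11.2 | 10.0–11.3 |
| Most favourable of three additive forms | 6.4 | 7.1 | 6.1 |
| Same, plus two ratio forms | 6.5 | 7.1 | 6.2 |
| Most favourable of all six | 11.8 | 13.1 | 12.4 |

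A repeat simulation with 60 per arm and three assumed processes gave 5.1% to 6.3% for the first rule, 9.6% to 11.9% for the second, and 12% to 13% for the most favourable form.

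**Where the excess arises.** Adding the ratio forms raises the rate by less than 0.1 point. Adding the unstructured common effect raises it by 5.3, 6.0 and 6.2 points.

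The reason shows in the overlap between that effect and the month-18 difference. At least one of the two rejects in 10.6%, 11.5% and 11.6% of trials. By subtraction both reject in about 0.3% (5.2 + 5.7 − 10.6), 0.4% (5.46 + 6.38 − 11.46) and 0.4% (5.34 + 6.72 − 11.62). Independent tests would give about 0.3% to 0.4%. Under the null the two contrasts behave almost as unrelated tests.

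**The case against.** The strongest reply is that the plan chooses by fit and not by significance, so the most-favourable-form rate is a ceiling and not a forecast. That stands. With the visit average as the fallback, the excess is at most about 1.5 points. The unstructured common effect already rejects 5.7% to 6.7% when fixed in advance, so part of the larger figures is a small-sample effect and not selection. With complete data and no interaction, categorical and linear time give the same arm contrast for a given covariance, so not every listed choice matters. A negative binomial model would also be defensible for a count with many zeros if it were fixed beforehand.

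A reader might infer more than the text supports:
- **Covariance structures as further free choices.** Autoregressive and exchangeable structures come in only if the unstructured model fails to converge, not on the strength of the plots, so they do not add to the selection.
- **A test of slopes.** The plan tests a difference in marginal means and does not offer a slope test.
- **A contradiction with "All hypothesis tests are pre-specified so there is no compelling reason to adjust the alpha level for multiple comparisons".** That sentence sits under Secondary outcomes analysis and concerns adjustment across hypotheses. It makes no claim about model form.
- **An unblinded analyst.** Study limitations says participants and study staff cannot be blinded because of the intervention. It does not say whether the analyst sees arm labels.

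None of this removes the core point. The plots are by arm, no default or rule is given, and no time point is named for the primary contrast.

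**Conclusion.** The concern holds: the nominal 5% is not guaranteed, and the tested quantity is not settled until the outcome has been seen by arm. It would be too strong to say that the test has one particular inflated error rate. A reasonable range is about 5% to 12% under the selection rules examined, and about 13% if the most favourable form is taken. These figures rest on assumed employment processes, on a p-value rule standing in for visual judgement, and on participant-level equivalents of the mixed models; the documents supply none of these.

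The change of estimand needs no simulation. Both arms start at zero cumulative weeks, so a sustained effect must widen over time. The case for an arm-by-visit term therefore follows from the design and needs no plots.

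**What to change.** Before any outcome is viewed by arm, state one primary model: a single fixed scale, visit as categorical, an arm-by-visit term, and the month-18 marginal-mean difference in weeks as the only contrast tested at 5%. An additive scale matches the difference in means on which the power rests. List the negative binomial, linear-time and no-interaction versions as sensitivity analyses. If checks of distribution or time shape are wanted, make them on plots pooled over arms.

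The cost is wording and less freedom to tailor the model. The 120 randomized and the stated power (81.5% by the normal approximation, 54 per arm, d = 0.55) do not change. The article reports 41 randomized, enrollment still open and no outcomes presented, so at that stage the change could be made ahead of the results.

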Harrison and colleagues conducted a systematic review of IPS for persons with substance use disorders (SUD) [15]. Their results yielded five randomized controlled trials (RCTs) and two studies that were non-randomized controlled trials [16–20]. Of the RCTs, only one included a specific sample with OUD as opposed to other types of SUD [16]. The other six studies evaluated IPS among samples with co-occurring mental illness and SUD [17–20]. Those with OUD specifically were not reported or separated in analyses from other SUDs. Nonetheless, across all of the RCTs, IPS participants had better employment outcomes than control groups. Of note, two of the RCTs were with a veteran sample [18, 20]. Among the two non-randomized IPS studies, participants obtained employment at higher rates of employment than the general rate of employment for individuals with co-occurring SUD within the state the study was conducted in [21]. Results of the non-randomized study showed that IPS participants with and without SUD obtained competitive employment at similar rates [22].

Lones and colleagues evaluated the efficacy of IPS for 45 patients with OUD enrolled in a methadone treatment program [16]. This is the only study found to evaluate IPS among an OUD population. Participants were randomized to either receive a 6-month IPS intervention or to a waitlist. During the 6-month intervention period, half of the IPS group attained competitive employment compared to only 5% among the waitlist control, which increased to 22% after 12-months but stayed at 50% for the IPS group.

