VA Service-Connected Disability Status						
None	10	40.0	6	37.5	16	39.0
Filing for the first time	2	8.0	1	6.3	3	7.3
Filing for appeal	–	–	1	6.3	1	2.4
Receiving any SC disability	10	40.0	8	50.0	18	43.9
Filing for increase	3	12.0	–	–	3	7.3
Receiving 100% SC	6	24.0	3	18.8	9	22.0
Employment Status						
Unemployed	21	84.0	14	87.5	35	85.4
Underemployed	4	16.0	2	12.5	6	14.6
Number of Competitive Jobs Held in the Last 3 Years						
Zero	12	48.0	8	50.0	20	48.8
One	4	16.0	5	31.3	9	22.0
Two	6	24.0	–	–	6	14.6
Three or more	3	12.0	3	18.8	6	14.6
Financial Dependents						
Zero	3	12.0	1	6.3	4	9.8
One	10	40.0	9	56.3	19	46.3
Two	5	20.0	5	31.3	10	24.4
Housing						
Single-family Home	6	24.0	4	25.0	10	24.4
Mobile Home	1	4.0	1	6.3	2	4.9
Apartment or Condominium	5	20.0	2	12.5	7	17.1
Renting Room	3	12.0	1	6.2	4	9.8
Transitional housing	3	12.0	3	18.7	6	14.6
Homeless shelter	3	12.0	4	25.0	7	17.1
Motel	1	4.0	–	–	1	2.4
Residential Treatment	3	12.0	1	6.3	4	9.8
Locality						
Urban	19	76.0	13	81.3	32	78.0
Rural	4	16.0	3	18.8	7	17.1
No response	2	8.0	–	–	2	4.9

*SSI* Social Security Income, *SSDI* Social Security Disability Income, *SC* Service-Connected

**Table 3 Tab3:** Baseline Opioid Use and Treatment History

Variable	IPS (*N* = 25)		Non-IPS-VR (*N* = 16)		Total (*N* = 41)	
	*M*	*SD*	*M*	*SD*	*M*	*SD*
Duration of OUD (years)	10.2	7.9	10.4	12.7	10.3	9.8
	Frequency	Percent	Frequency	Percent	Frequency	Percent
Types of Opioids Used						
Prescription pain pills	19	76.0	11	68.8	30	73.2
Street-derived pills	10	40.0	8	50.0	18	43.9
Street-derived IV, not heroin	2	8.0	1	6.3	3	7.3
Heroin	8	32.0	5	31.3	13	31.7
Current OUD Treatment (past 12 months)						
Any Treatment	21	84.0	10	62.5	31	75.6
Medications for OUD	12	48.0	4	25	16	39.0
Other psychotropic medication	3	12.0	1	6.3	4	9.8
Supportive group therapy	9	36.0	3	18.8	12	29.3
Supportive individual therapy	8	32.0	7	43.8	15	36.6
Complimentary	3	12.0	1	6.3	4	9.8
Inpatient	1	4.0	2	12.5	3	7.3
Residential	5	20.0	5	31.3	10	24.3
Outpatient	2	8.0	2	12.5	4	9.8
OUD Treatment prior to 12 months						
Any Treatment	18	72.0	9	56.3	27	65.8
Medications for OUD	9	36.0	6	37.5	15	36.6
Other psychotropic medication	2	8.0	1	6.3	3	7.3
Supportive group therapy	8	32.0	6	37.5	14	34.1
Supportive individual therapy	8	32.0	8	50.0	16	39.0
Complimentary	1	4.0	3	18.8	4	9.8
Inpatient	6	24.0	4	25.0	10	24.4
Residential	5	20.0	4	25.0	9	22.0
Outpatient	2	8.0	–	–	2	4.8
MINI International Neuropsychiatric Interview						
Major Depressive (current)	3	12.0	1	6.3	4	9.8

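### The negative binomial option for the primary outcome, fitted with participant random effects, would report LS-means well below the weeks the arms actually worked, so it does not estimate the difference in means that the trial is powered for

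*Protocol article*

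**What the plan says.** All of this is in the protocol article, mostly under Primary outcome analysis.

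- The dependent variable is the cumulative number of competitive weeks at each of the nine follow-up assessments. Participant and site are random effects. Weeks without data count as not worked.
- The model is chosen after looking at longitudinal plots by group, according to whether the effect "appears to be additive (linear regression) or multiplicative (suggesting negative binomial regression").
- The primary hypothesis "will be evaluated using predicted marginal means (i.e., LS-means) to estimate the difference" between arms, and the plan will "test significance at the *p* < 0.05 level".
- The sample size rests on a mean difference: 54 analysable participants per group give 80% "power to detect a difference in means between groups of 0.54 standard deviations for a continuous outcome".

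The article gives no expected share of participants with zero weeks. Two places bear on it:

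- The Introduction describes the one cited trial in OUD, where during the six-month intervention "half of the IPS group attained competitive employment compared to only 5% among the waitlist control". At 12 months the figures were 50% and 22%.
- Table 2, under "Number of Competitive Jobs Held in the Last 3 Years", shows 20 of 41 participants (48.8%) with none.

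**The concern.** The question is whether the negative binomial branch, as specified, estimates what the trial sets out to estimate. It would arise even if that model had been fixed in advance.

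The outcome has a ceiling, which the negative binomial lacks, and probably a pile-up at zero. With a log link and a participant random intercept, people who never work can be fitted only by very low intercepts, which inflates the between-person variance. An LS-mean at random effect zero is then the expected count for a participant at the middle of that wide distribution. It is not the arm's mean number of weeks.

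The branch is a live possibility because cumulative counts fan out by construction. Suppose the arms work at constant rates that end at 22 and 35 weeks. The ratio is 1.6 at every visit, while the difference grows from 13/9 = 1.4 weeks at month 2 to 13 at month 18. On the planned plots that would look multiplicative. The headline result could then give mean weeks that neither arm worked, and a ratio several times too large.

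**Working it through.** **1. The plan's own figure.** Inputs from the article: "The target sample size is 120 randomized participants (60 per study arm"), and "assuming that only 90% provide analyzable data this yields approximately 54 participants per group". Alpha is 0.05, taken as two-sided. Power = Φ(d·√(n/2) − 1.96).

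- d = 0.55: Φ(0.55 × √27 − 1.96) = Φ(0.898) = 81.5%.
- d = 0.54: Φ(0.54 × √27 − 1.96) = Φ(0.846) = 80.1%.

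Both stated figures are reproduced. They refer to a difference in means.

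**2. Range of the outcome.** 18 × 52.18/12 = 78.3 weeks. (Under Employment outcome assessments, half the active follow-up is put at 32 weeks, which implies 64. That is a separate inconsistency; the outcome is bounded either way.)

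**3. What the LS-mean estimates.** With E[Y | u] = exp(β + u) and u ~ N(0, σ²):

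- LS-mean at u = 0: exp(β), the median participant.
- Mean over participants implied by the model: exp(β + σ²/2).

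The two agree only when σ is small.

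**4. Simulation.** Weekly job histories over 78 weeks, 54 per arm, with a never-employed fraction, calibrated to d of about 0.55. The model was a negative binomial with participant random intercept and arm by categorical visit; gender and site were left out. Zero shares are assumptions, varied widely. Entries are control / IPS at month 18. LS-means and σ are medians over 20 to 58 fits per row.

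| Zeros | Mean weeks | LS-means | True ratio | Ratio of LS-means | σ |
|---|---|---|---|---|---|
| 78% / 50% | 12.7 / 29.1 | 0.0 / 0.3 | 2.3 | not meaningful | 6.4 |
| 60% / 40% | 17.2 / 37.2 | 0.07 / 2.0 | 2.2 | about 29 | 5.2 |
| 50% / 30% | 21.8 / 39.1 | 0.6 / 4.8 | 1.8 | 7.8 | 4.3 |
| 40% / 20% | 27.3 / 42.1 | 2.1 / 12.9 | 1.5 | 6.2 | 3.3 |
| 25% / 10% | 30.7 / 44.9 | 8.5 / 23.7 | 1.5 | 2.8 | 2.3 |
| 15% / 5% | 29.0 / 42.3 | 11.4 / 31.5 | 1.5 | 2.8 | 1.8 |

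Both LS-means are too low in every row. Their difference is wrong in no fixed direction. At 50%/30% the median difference is 4.4 weeks against a true 39.1 − 21.8 = 17.3. At 15%/5% it is 31.5 − 11.4 = 20.1 against 13.3. At 25%/10% it is 15.2 against 14.2, close only by coincidence.

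**5. Mechanism, in the 40%/20% row.** Put β = ln 2.10 and ln 12.94 with σ = 3.32, and treat the counts within a person as Poisson. The model then implies 36% and 19% zeros, close to the simulated shares. It also places 14% of control and 29% of IPS participants above 78 expected weeks: P(Z > (ln 78 − β)/σ). It matches the zeros by spreading the distribution beyond what is possible.

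**6. Averaging over the random effect does not repair it.** exp(β + σ²/2) gives 2.10 × exp(5.51) ≈ 520 weeks for control and about 3,200 for IPS at 40%/20%. At 15%/5% the simulated medians were 52 and 143, against true means of 29 and 42.

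**The case against.** Several points on the other side have force.

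- **The branch is a contingency.** The power statement and the steady-worker analysis both point to linear regression as the reference. This stands: harm follows only if the plots lead to the negative binomial model.
- **The zero share is not known.** The cited trial had 45 methadone patients and a waitlist control. Here the control is active vocational rehabilitation and everyone wants competitive work. Table 2 reports history before enrolment. All this is fair, but the distortion remains at 15%/5% zeros, far below either indicator.
- **The implementation is open.** The article also mentions an unstructured, autoregressive or exchangeable covariance for the repeated outcomes. A version without a log-scale participant intercept could give population-averaged means. However, the article does name participant as a random effect, and that is what was simulated.
- **The team would notice.** An LS-mean of 2 weeks beside an observed 27 is conspicuous. Replacing the primary estimate at that stage would be a post hoc change.

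A reader might go further and infer that a negative binomial model without participant effects loses most of the stated power. The article does not support that, because no such model is planned. Fitted to the single 18-month total with model-based standard errors, power does fall to 11–15% at zeros of 40%/20% and above. With robust variance the same fit keeps 77–82%.

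Nor has the test in the planned branch been shown to fail. Null rejection was 0–12% and power 69–86%, in only 27 to 58 replicates per scenario, which is too few to judge.

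**Conclusion.** The point holds as one about the quantity estimated. If the negative binomial branch is taken with a participant random intercept, the month-18 LS-means do not estimate mean weeks worked in either arm. They were too low at every zero share tried, from slightly (31.5 against 42.3 in IPS at the lowest share) to almost entirely. The ratio of the arms was inflated from about 1.5 to between 2.8 and 6.2 where zeros ran from 15%/5% to 40%/20%, and by more above that. The difference in mean weeks, on which the 80% power rests, is not what this branch delivers.

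The sizes depend on assumed zero shares, a random-intercept form without gender or site, and few fits per scenario. The direction of the error in the LS-means did not depend on the zero share. No claim is made about lost power or false-positive rate under the plan.

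**What to change.** State that, whatever the plots show, the primary test is the difference between arms in mean competitive weeks at 18 months, on the linear scale, with heteroscedasticity-robust (sandwich) standard errors. The plots can still inform how time is described.

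If a relative effect is wanted, report as supportive the ratio of the arms' mean weeks from a log-link model of the single 18-month total, again with robust standard errors. State that back-transformed LS-means from a log-link model with participant random effects will not serve as the primary estimate.

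This changes analysis wording only. On the simulated data a t-test of mean weeks kept 78–83% power, in line with the stated design. The article reports no outcomes and enrolment was still open, so nothing in it stands in the way of the change. The small price is giving up a fully model-based ratio test.

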### Randomization and follow-up schedule

Participants who meet eligibility criteria are randomized (1:1) to either IPS or non-IPS-VR. Randomization uses a permuted block design of randomly varying block sizes stratified by site. Once assignment is made, the participant is analyzed in that group regardless of future events or services rendered, in accordance with the intent-to-treat principle.

Once informed consent is obtained, baseline assessments are administered. Participants are assessed at baseline and every 2 months (months 2, 4, 6, 8, 10, 12, 14, 16) and then final assessment at month 18 for employment outcomes and secondary outcomes. At each research visit, participants are assessed for the occurrence of adverse events or serious adverse events. The 18-month follow-up period allows for start-up time involved in each intervention prior to establishing competitive work and allows enough time for a participant to establish steady competitive work and achieve the secondary outcome goals.

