### Employment outcome assessments

The primary outcome is the number of weeks worked during the 18-months following randomization. A “week worked” is defined as working either full- or part-time in a competitive job during a 7-day period. Competitive employment is defined as a job that pays at least minimum wage based on wages, salary, or commission, is in a setting not set aside for those with mental illness or disabilities, and is not transitional work. The exploratory employment outcome will be ‘steady worker’ status, defined as obtaining competitive employment for at least 50% of the active follow-up period (i.e. ≥ 32 weeks). Longitudinal employment data will include number of weeks, days, and hours worked in a competitive job, dollars earned, type of job(s), number of jobs, and job satisfaction. Job satisfaction is measured with the Indiana Job Satisfaction Scale (IJSS) [33]. Employment outcomes and IPS or non-IPS-VR services received will be collected using a calendar approach and verified by copies of pay documents (e.g., pay stub, direct deposit notices, pay checks).

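### The primary contrast is stated in hours, is not tied to month 18 and may fall back on equal-variance covariances, so as written it need not estimate the 18-month difference in weeks

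*Protocol article*

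**What the plan says.** The outcome is one total per participant. Under Employment outcome assessments: "The primary outcome is the number of weeks worked during the 18-months following randomization". Under Primary outcome analysis: "The primary employment outcome is the number of weeks with competitive employment over the 18-month follow-up period". The hypothesis is that "participants randomized to IPS will work more weeks over the 18-months compared to those randomized to non-IPS-VR".

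The model is longitudinal, "considering the cumulative number of weeks worked at each assessment as the dependent variable", with study arm as the main independent variable and adjustment for gender. Site and participant are both random effects. The schedule gives nine post-baseline values: "Participants are assessed at baseline and every 2 months (months 2, 4, 6, 8, 10, 12, 14, 16) and then final assessment at month 18".

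The covariance of the repeated outcomes is first specified "as unstructured and will proceed respectively to autoregressive and exchangeable structures if convergence issues are encountered". The coding of time and the inclusion of a group-by-time term are decided after looking at plots by group.

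The primary hypothesis "will be evaluated using predicted marginal means (i.e., LS-means) to estimate the difference in hours worked and test significance" at the 0.05 level. No visit is named for these means. For the secondary outcomes one is: "We will formally test for differences in outcomes at 18 months using predicted-marginal means".

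Weeks without employment data are scored as not worked.

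**The concern.** Three features of the text meet in the single primary p-value.

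- **Unit.** The estimate is in hours, while the outcome, the hypothesis and the dependent variable are in weeks. Elsewhere in the analysis plan hours worked is only one of several further descriptive outcomes.
- **Target.** Cumulative weeks are zero in both arms at randomization and separate afterwards. A marginal mean for arm equals the 18-month mean only if the model contains arm by time and the contrast is taken at month 18. The text guarantees neither.
- **Standard error.** Standard autoregressive and exchangeable structures assume the same variance at every visit. A running total does not behave that way.

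Different permitted routes therefore test different quantities, and some give a wrong standard error. The choice among them depends partly on plots of the outcome by arm.

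**Working it through.** **1. The plan's own power.** Inputs from Primary outcome analysis: 60 per arm, 90% analyzable (60 × 0.9 = 54), d = 0.55 or 0.54. Two-sided alpha of 0.05 is assumed, since sidedness is not stated. Power = Φ(d√(n/2) − 1.96).

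- d = 0.55: Φ(0.55 × √27 − 1.96) = Φ(0.898) = 0.815.
- d = 0.54: Φ(0.54 × √27 − 1.96) = Φ(0.846) = 0.801.

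Both stated figures reproduce (0.808 and 0.794 with the noncentral t). They belong to a two-sample comparison of one value per participant, which matches the 18-month total.

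**2. Averaging over visits.** Number the visits k = 1 to 9, at month 2k. With a constant weekly difference, the gap at visit k is (k/9)Δ, where Δ is the 18-month difference. The average is (1 + 2 + … + 9)/(9 × 9) = 45/81 = 5/9 = 0.56 of Δ. With an assumed start-up lag of L months, the average of max(2k − L, 0)/(18 − L) is 0.50, 0.44 or 0.39 for L = 2, 4 or 6.

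**3. Growth of the variance.** Eighteen months is 78 weeks, so at month 2 nobody can exceed 78/9 = 8.7 weeks, and the SD cannot exceed half of that, 4.3. If the month-18 SD were no larger, the planned 0.54 SD would be only 0.54 × 4.3 = 2.3 weeks out of 78. A much larger month-18 SD is therefore to be expected.

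If SD grows in proportion to time, the variance pooled over visits is the mean of (k/9)² = 285/729 = 0.391 of the month-18 variance. A month-18 contrast using the pooled variance has a standard error √0.391 = 0.625 of the correct one. Its type I error is 2[1 − Φ(1.96 × 0.625)] = 0.22.

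**4. Simulation of the permitted routes.** 1,500 null and 1,500 alternative trials, 54 per arm, with weekly job starts and losses that vary between people. The rates are assumptions, tuned to d of about 0.55 at month 18. The true month-18 difference is 14.0 weeks, and the control SD rises from 1.9 weeks (month 2) to 23.3 (month 18).

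| Route | Mean estimate, weeks | Model SE / true SE (null) | Type I error | Power |
|---|---|---|---|---|
| Unstructured, arm by visit, month 18 | 14.1 | 1.02 | 4.2% | 81% |
| Exchangeable, arm by visit, month 18 | 14.1 | 0.62 | 23% | not meaningful |
| Autoregressive, arm by visit, month 18 | 14.1 | 0.71 | 17% | not meaningful |
| Exchangeable, averaged over visits | 7.2 | 1.02 | 3.9% | 81% |
| Autoregressive, averaged over visits | 7.2 | 1.34 | 0.3% | 60% |
| Unstructured, no arm by time | 0.1 | 0.88 | 8.3% | 8% |

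A random intercept with linear time and a month-18 contrast, which the text also allows, gave 28% type I error. The last row is near zero because the fit puts weights of 1.61, −0.73 and 0.16 on months 2, 4 and 6 and almost none on later visits.

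Two further simulations with assumed job rates agree:

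- **60 per arm:** month 18 gave 13.4 weeks, 4.9% type I error and 80% power. The visit average was 7.1 weeks. Unstructured without interaction gave 0.1 week and 8.5% power. Month-18 type I error was 22.5% (exchangeable) and 17.6% (autoregressive).
- **54 per arm:** month 18 gave 13.8 weeks, 4.7% and 80%. The visit average was 7.3 weeks. Unstructured without interaction gave 0.15 week and 10% power. Month-18 type I error with pooled variance was 21%.

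**The case against.** The strongest reply is that the natural reading is sound. The hypothesis is about weeks over 18 months, the dependent variable is cumulative, and the secondary models, described as similar, are tested at 18 months. The first-choice covariance with arm by time and a month-18 contrast performs as planned. Hours looks like a drafting slip. A journal article may also leave the visit of the contrast to a statistical analysis plan that is not shown.

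Much of this stands. A reader might infer that the plan averages the means over the nine visits and so cannot estimate the 18-month difference. The article does not say so; it leaves the visit open. The silence alone would not be a finding.

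Three further limits also stand:

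- The plot check would usually lead to an arm-by-time term. In 1,000 simulated trials with a weekly hire rate of 5% against 2%, the month-18 gap exceeded three times the month-2 gap in 99%. The near-zero route is permitted but improbable.
- The exchangeable visit average is a valid test with about 79 to 81% power. Its fault is that it answers a different question.
- A participant random effect on top of an unstructured covariance is redundant and may invite convergence trouble, but no convergence rate was examined. The negative binomial option was not simulated either.

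The reply does not remove what the article itself fixes: the wrong unit, an interaction made optional on plots by arm, and equal-variance fallbacks for a cumulative outcome.

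**Conclusion.** The point holds in conditional form. The stated unit contradicts the outcome and hypothesis, and the primary test as written need not estimate the 18-month difference in weeks.

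The size depends on the route. Averaging over visits gives 5/9 of the difference, which requires only equal visit spacing and a constant weekly difference; simulation gives about half. Omitting the interaction under unstructured covariance gives almost nothing.

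The standard-error fault is confined to a month-18 contrast after a fallback. The figure of about 22% in closed form assumes SD proportional to time, and the range of 17 to 23% rests on assumed job rates. A reader might infer that the primary test is generally anti-conservative. That is not supported: the unstructured month-18 contrast is sound, and autoregressive averaging errs the other way.

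**What to change.** Revise Primary outcome analysis as follows:

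- Replace hours with weeks.
- Define the primary estimate as the IPS minus non-IPS-VR difference in mean cumulative competitive weeks at month 18.
- Prespecify arm by categorical visit with an unstructured within-participant covariance and no additional participant random effect, and drop the plot-based choice of interaction and time coding.
- Replace the autoregressive and exchangeable fallbacks with heterogeneous-variance structures plus robust standard errors.

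A simpler alternative is to regress each participant's 18-month total on arm, site and gender. That total always exists, because missing weeks are scored as not worked, and it matches the comparison behind the stated power.

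The cost is wording only, with no new data or visits. The change should be made before outcome data are plotted by arm.
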